## Abstract

**Introduction:**

Global population ageing is one of the key factors linked to the projected rise of dementia incidence. Hence, there is a clear need to identify strategies to overcome this expected health burden and have a meaningful impact on populations’ health worldwide. Current evidence supports the role of modifiable dietary and lifestyle risk factors in reducing the risk of dementia. In South-East Asia, changes in eating and lifestyle patterns under the influence of westernised habits have resulted in significant increases in the prevalence of metabolic, cardiovascular and neurodegenerative non-communicable diseases (NCDs). Low vegetable consumption and high sodium intake have been identified as key contributors to the increased prevalence of NCDs in these countries. Therefore, nutritional and lifestyle strategies targeting these dietary risk factors are warranted. The overall objective of this randomised feasibility trial is to demonstrate the acceptability of a dietary intervention to increase the consumption of high-nitrate green leafy vegetables and reduce salt intake over 6 months among Malaysian adults with raised blood pressure.

**Methods and analysis:**

Primary outcomes focus on feasibility measures of recruitment, retention, implementation and acceptability of the intervention. Secondary outcomes will include blood pressure, cognitive function, body composition and physical function (including muscle strength and gait speed). Adherence to the dietary intervention will be assessed through collection of biological samples, 24-hour recall and Food Frequency Questionnaire. A subgroup of participants will also complete postintervention focus groups to further explore the feasibility considerations of executing a larger trial, the ability of these individuals to make dietary changes and the barriers and facilitators associated with implementing these changes.

**Ethics and dissemination:**

Ethical approval has been obtained from Monash University Human Research Ethics Committee and Medical Research and Ethics Committee of Malaysia. Results of the study will be disseminated via peer-reviewed publications and presentations at national and international conferences.

ISRCTN47562685; Pre-results.

Strengths and limitations of this studyFeasibility of the first 2×2 trial testing single and combined effects of dietary nitrate and salt reduction for the prevention of cognitive decline in developing countries.Longest high-nitrate-based intervention ever conducted.Use of objective biomarkers for the assessment of adherence to the dietary intervention and internal validation of the dietary assessment methods used (urinary sodium—24-hour urine vs spot urine/nitrate levels in blood—dried blood spots vs plasma and ELISA vs gold standard/nitrate in saliva—salivary strip (point of care test) vs ELISA using saliva samples).Mixed-method approach to obtain key information on the feasibility of the dietary intervention.Owing to the small sample size and the feasibility nature of this study, the planned comparative analysis is only exploratory, and therefore, the efficacy of the intervention between groups cannot be determined. However, the results of this study will be instrumental in the design and calculation of the sample size of a larger, follow-on efficacy trial.

## Introduction

Dementia is characterised by multiple cognitive deficits and loss of independence, and its pathogenesis is linked to multiple distinct neuropathological processes including Alzheimer’s disease and/or vascular pathology.^1^ Several of the pathological processes underlying dementia might be delayed, or prevented, by interventions focused on dietary and behavioural changes^2^ and, in the absence of definite pharmacological treatments, these options represent a key strategy to alleviate its individual and social impact.^3^ Optimal control of modifiable cardiovascular factors, such as blood pressure, and adherence to lifestyle recommendations have been consistently associated with reduced dementia risk in observational studies.^2–4^ The role of nutrition for dementia prevention has been extensively investigated by testing the role of single nutrients (ie, n-3 Poly Unsaturated Fatty Acids or B vitamins^5^) or dietary patterns (ie, dietary approaches to stop hypertension (DASH) diet^6^ or Mediterranean diet^7 8^). There are a small number of randomised controlled trials (RCTs) available to support the effect of diet on cognition in mild cognitive impairment^9^ and among those at risk of cognitive decline or cognitively healthy populations^10^; however, the trials have a small sample size and overall modest quality.

Malaysia is experiencing rapid socioeconomic and nutritional transitions.^11^ Changes in individual eating and lifestyle patterns and rise in food availability and financial prosperity of the population have resulted in significant increases in the prevalence of chronic metabolic, cardiovascular and neurodegenerative non-communicable diseases (NCDs).^12^ Effective public health interventions for the prevention of dementia are challenging in countries with limited social and healthcare resources which are unable to meet the growing demands of ageing populations. A systematic review of 22 RCTs investigated the effect of nutritional interventions on cognitive performance in developing economies of East Asia, and the majority of the studies showed some significant beneficial effects of the nutritional interventions on cognitive performance. However, these effects were not consistent across all of the neuropsychological tests used in each study.^10^ Therefore, there is a need for well-designed nutritional intervention studies for the early prevention of cognitive decline and dementia.

Recent analyses have identified inorganic nitrate as a potential nutrient improving vascular and metabolic health.^13^ Beetroot and green leafy vegetables, such as spinach, lettuce and rocket, are a key source of naturally available inorganic nitrate, containing over 250 mg of nitrate per 100 g of fresh vegetable weight.^13^ Inorganic nitrate is closely linked to the metabolism of nitric oxide (NO) which is known for its multiple effects on physiological functions such blood pressure, brain function and immunity.^14^ An increase in inorganic nitrate consumption has been associated with an increase in NO production via complex mechanisms involving oral microbiota, gastric environment and activation of reducing enzymes.^15^ Recent epidemiological studies and clinical trials have demonstrated the association of increased nitrate intake with improved blood pressure, metabolic health and cognitive function.^14 16^ A 15-year prospective cohort study investigated the association of consumption of high-nitrate vegetables and risk of atherosclerotic vascular disease (ASVD) mortality. Results showed that a consumption of approximately 30 mg/day higher nitrate intake from vegetables was associated with a 21% lower risk of ASVD mortality. This nitrate amount equates to approximately 10–30 g/day of nitrate-rich vegetables.^17^ However, the impact on cognition is still unknown with studies of short intervention durations and among small samples, and limited studies conducted in developing countries.^13 14^ Nevertheless, with hypertension highlighted as an important modifiable risk factor for dementia,^3 18^ more studies that test the implementation of dietary interventions that aim to improve blood pressure are warranted.

Sodium is the main electrolyte contained in extracellular fluids and involved in regulation of blood pressure and cellular activities. An excess sodium intake has been linked to extracellular volume expansion and increased blood pressure.^19^ The DASH diet has been specifically developed to promote consumption of healthy dietary choices alongside strictly controlled sodium intake.^20^ Secondary analyses derived from seminal DASH studies showed additional benefits on blood pressure and cardiometabolic health in individuals with lower salt intake and adherence to a healthy dietary pattern.^21^ These analyses have been extended to cognitive function with promising results,^22 23^ but the evidence has mostly come from studies conducted in the USA and no studies to our knowledge have been conducted in low/middle-income countries (LMICs). Epidemiological studies have repeatedly proven the association of high salt diets with impaired blood pressure control and increased cardiovascular risk^24 25^; this evidence has been confirmed in several clinical trials testing the effects of salt-reducing interventions and demonstrating the protective effects of salt reduction on cardiovascular health.^26 27^ A prospective study looked at the relationship between a reduction in salt intake with blood pressure, mortality from stroke and ischaemic heart disease (IHD).^28^ A decrease in salt intake by 1.4 g/day, as measured by 24-hour urinary sodium, contributed to a reduction in stroke and IHD mortality, and in addition, among individuals who were not on antihypertensive medication, there was a significant fall in systolic blood pressure (SBP) of 2.7±0.34 mm Hg.^28^ Excessive sodium consumption is recognised as a global health issue^29^ with efforts aiming to reduce salt intake at the population level by 30% by 2025. Seventy-five countries have already implemented national sodium reduction programmes to help meet this target.^30^

In sum, an increased consumption of dietary nitrate and lower salt intake may have additional benefits on health outcomes such as blood pressure and cognition, mediated by an increase in NO generation (ie, nitrate) and control of vascular tone and cellular metabolism (ie, sodium). However, this hypothesis has never been tested in previous interventions which represents the main aim of the feasibility study proposed in this protocol. The Global Health Dementia Prevention and Enhanced Care (DePEC) project is a National Institute for Health Research (NIHR) funded study with a key goal to develop approaches for dementia prevention and develop more efficient postdiagnostic care in LMICs. The DePEC-Nutrition feasibility study (presented here) is one of five work streams within the overall DePEC project.

### Purpose and aims

The overall objective of the DePEC-Nutrition feasibility study is to demonstrate the acceptability of a dietary intervention to increase the consumption in high-nitrate green leafy vegetables and reduce salt intake over a 6-month period among Malaysian adults with raised blood pressure. The objectives focus on the core areas of a trial that need to work for the study to succeed procedurally, such as recruitment ability and participant retention, data collection procedures and assessment methods used, potential to deliver the dietary intervention and resource requirement. Information on the effect size of the intervention on cognition and blood pressure will also be determined, which will be instrumental in the design and calculation of the sample size of a follow-on efficacy trial.

## Methods and analysis

### Study design

The DePEC-Nutrition feasibility study is a 6-month randomised 2×2 factorial trial including four parallel arms: (1) control, (2) high-nitrate vegetable consumption, (3) low salt consumption and (4) combined high-nitrate vegetable consumption plus low salt consumption. The trial will be conducted among 120 middle-aged and older Malaysian adults. Sponsor and grant number: GHR Group: 16/137/62—NIHR Global Health Research Group on DePEC, Newcastle University, UK. The Standard Protocol Items: Recommendations for Interventional Trials reporting guidelines were used to guide the preparation of this protocol.^31^

### Participants

This study is embedded within the South East Asia Community Observatory (SEACO) population (http://www.seaco.asia/). SEACO is a health and demographic surveillance site (HDSS); a unique research platform in population health and well-being focused on a middle-income community in Segamat, Johor in the southern tip of the Peninsular Malaysia. The district of Segamat comprises urban, rural and plantation areas with an ethnic mix including Malays, Chinese and Indian, in similar proportions to the national population. SEACO runs its HDSS research platform in five subdistricts (mukim) of the Segamat district: Bekok, Chaah, Gemereh, Jabi and Sungai Segamat. The SEACO population was established using a baseline census (March 2012 to February 2013) that included information on sociodemographic status and self-reported health conditions. Consenting participants underwent detailed health profile assessments in the first health round in 2013–2014. The next census was done in 2017, with a total number of 40 015 participants completing the assessment. Individuals were seen again after 1 year (in 2018) for the second health round. Individuals aged 50 years and over, who are living in Segamat, Johor and have been assessed as part of SEACO during the health round in 2018 will form the study population for the DePEC-Nutrition feasibility study. The baseline assessment will be carried out in the Klink Kesihatans (KK) in Sungai Segamat subdistrict (a community health clinic in Segamat, Johor). Hence, only participants from within 5 km radius of KK Segamat will be included in the study population. A total of 2433 participants have been identified on the database as potentially eligible for this study by broad application of the study criteria (mean age (SD): 61.27 (6.77) years and number of men: n=1078 (44.3%)). This subset of participants will be screened in detail, and then will be informed of the study and invited for a screening visit as outlined in the study procedures.

### Recruitment

The community will be informed about this study via a local Community Engagement Committee who meet regularly to distribute information on projects planned within SEACO. Participants will be randomly identified by the application of the inclusion and exclusion criteria to the SEACO health surveillance database. Potential participants will be approached via a home visit and will be provided with information about the study. They will be given an opportunity to read detailed information about the study procedures and can ask questions. Thereafter, their interest of participating in the study will be evaluated. If they agree to take part, a screening assessment will be completed. If eligible, participants will be invited to attend a baseline study visit at the health facilities within the community.

### Eligibility criteria

To be eligible for inclusion in this study, participants must report as:

Male and female participants with an age between 50 and 75 years from the SEACO database.Pre-hypertensive, stage 1 hypertensive or diagnosed hypertensive: any person with a self-reported history of hypertension (on or not on medication) or with elevated blood pressure (SBP 120–159 mm Hg or diastolic blood pressure (DBP) 80–99 mm Hg).Not severely cognitively impaired (defined as a Mini Mental Examination Status (MMSE) Score of 19 or over).

Participants will be excluded from the study if they:

Are participating in other research clinical studies.Are unable to provide consent.Have SBP more than or equal to 160 mm Hg and/or DBP more than or equal to 100 mm Hg.Adhere to any therapeutic diet such as weight loss treatments or a gluten-free diet.Are vegan (these individuals are likely to have a high intake of vegetables). Since Indian participants are more likely to follow a vegetarian or semi-vegetarian diet, in order to maintain representativeness across ethnic groups included in the study, only participants who are vegan will be excluded from the study.Participants with a body mass index (BMI) less than 18.5 kg/m^2^.Have a history of active cancer or any diagnosis of cancer in the last 5 years.Have a history of excessive alcohol intake (>21 units of alcohol per week).Have a history of brain damage or significant head trauma (resulting in a loss of consciousness).Have a diagnosis of acute and chronic medical conditions interfering with the study outcomes such as systemic infections (tuberculosis, hepatitis B, HIV/AIDS), severe liver and kidney diseases, inflammatory bowel diseases, coronary heart diseases, cerebrovascular diseases or is a diabetic on insulin therapy.Have had any major surgical procedures (in the past 6 weeks or planned in the next year) that could interfere with the study outcomes.Have a current diagnosis of moderate or severe depression, or other serious mental or brain disorder and/or are currently on psychiatric medication (antidepressants, sedatives, antipsychotics).Regularly use sodium-altering drugs (ACE inhibitors, angiotensin receptor blockers, corticosteroids, diuretics, hormonal therapies (oestrogens, thyroxin and progesterone), non-steroidal anti-inflammatory drugs, proton-pump inhibitors), organic nitrates.Have changed their antihypertensive medication regimen in the previous 3 months.Have limited mobility due to any reason.Are planning to move house within a year.

### Study procedure

Data collection will be undertaken directly on an electronic hand held device (Samsung Galaxy Tab 3v—Survey CTO). Questionnaire items will be read out loud by the data collector, and participant responses will be recorded directly onto the electronic tablet. The flow of participants through the DePEC-Nutrition feasibility study is illustrated in figure 1. At the screening visit, written informed consent will be first obtained, after which participants will complete a screening questionnaire to collect information on demographics, comorbidities, medication history, cognitive function (MMSE), body weight, height and resting blood pressure. If eligible, participants will undergo baseline assessments, consisting of two parts: a home visit (part 1), followed by an appointment at KK, Segamat (part 2). Baseline assessments will include: obtaining respondent’s signed informed consent for study participation, eligibility assessment (medical and medication history), dietary assessment (24-hour recall and Food Frequency Questionnaire (FFQ)), cognitive assessment, collection of biological samples (blood, dried blood spots, 24-hour urine and spot urine samples, saliva samples and salivary strips), measurements of hand grip and gait speed, physical activity (International Physical Activity Questionnaire (IPAQ)) and depression (Geriatric Depression Scale (GDS)).

**Figure 1 F1:**
[figure not shown]
A flow diagram providing an overview of the study procedures.

An interim 2-month visit will take place for those in the intervention groups only, to provide reinforcement messages relating to the allocated dietary intervention and with a view to enhancing compliance with the intervention. In addition, a brief adherence questionnaire will be administered, body weight and resting blood pressure will be measured and salivary strip and spot urine samples will be collected. The same measurements and further dietary reinforcement messages will be conducted at an interim 4-month visit for the participants allocated to the intervention arms. Participants in the control arm will only have one interim visit at month 4 and will have their weight and blood pressure measured. The end of study visit (at KK, Segamat) will include the conduction of the measurements collected at baseline, including cognitive assessment, dietary assessment and collection of biological samples (blood, dried blood spots, 24-hour urine and spot urine samples, saliva samples, salivary strips). In addition, an exit group session (focus group evaluation) and a self-administered feedback questionnaire will be scheduled to evaluate the adherence to the interventions and obtain detailed feedback on the overall study protocol. Finally, the participants will be offered a token of appreciation to acknowledge their participation in the study and to compensate for travel expenses. This is usually to the value of RM 25.

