### Intervention and control arms

This dietary and behavioural intervention will focus on key components that are related to changing local dietary patterns influenced by nutritional transition trends in Malaysia. It aims to target two key components that have protective (dietary nitrate) and negative (salt intake) effects on cardiovascular and cognitive health. The intervention will target individuals with a higher Cardiovascular Disease (CVD) risk to adopt a tailored strategy to enhance daily consumption of green leafy vegetables and/or reduce salt intake. Nutritional counselling sessions with a medical doctor will be conducted at baseline to provide sustainable and effective strategies to improve dietary habits as well as monitor and address key barriers to dietary change. These sessions will be delivered in a group setting using PowerPoint slides and practical activities to educate the group on the allocated dietary intervention. All intervention groups will receive written information focused on health benefits, sources, recommended intakes and practical tips related to one of the following dietary interventions: (1) to increase dietary nitrate, (2) to reduce salt intake and (3) to increase dietary nitrate and to reduce salt intake. Those who are randomised to the salt intervention (either alone or combined) will receive a measuring spoon as an additional strategy to support individuals to understand portion size and measure salt intake, as successfully tested by an intervention study in China.^33^ Furthermore, the Ministry for Health Malaysia set out in their Salt Reduction Strategy 2015–2020 how reducing the amount of salt and sauces consumed in the home is a key priority.^34^ This provides justification for inclusion of the salt restriction spoon as an intervention strategy. The intervention groups will also receive bi-weekly text message reminders to provide reinforcement of the key dietary behaviour change messages relevant for their group allocation. Compliance will be monitored during the intermediate visits (2 and 4 months, respectively) where participants will also receive reinforcement video messages to remind participants of the key dietary advice that was discussed during the counselling sessions at baseline. Those allocated to the control group (4) will receive written information on general healthy eating and lifestyle advice based on the Malaysian dietary guidelines.^35^

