### Outcome measures

Outcome assessments will be conducted at baseline, month 4 and month 6 for all groups, with an additional assessment visit at month 2 for those in the intervention groups. Assessments at baseline and month 6 will be conducted in clinic/at home, with remaining assessments completed in the participants own home. The same instruments will be used for measurements at each time point. Assessors are trained prior to the assessments to follow a standardised protocol. A timeline of the study procedures can be found in table 1.

**Table 1 T1:** Timeline of study procedures

Procedures	Consent/screening	Baseline Week 1	Week 2	Week 4	Week 6	Week 8	Week 10	Week 12	Week 16	Week 18	Week 20	Week 22	End of study Week 24
Inclusion/exclusion	✓												
Consent	✓												
Activities for intervention group													
Dietary education		✓											
Reinforcement at home visit		✓				✓			✓				
Group education counselling session		✓											
Home visit						✓			✓				
SMS messages			✓	✓	✓	✓	✓	✓	✓	✓	✓	✓	✓
Activities for control group													
General health promotion message		✓											
Home visit									✓				
Study measurements													
Sociodemographic		✓											
Concomitant medication check list		✓				✓							✓
Any medical events		✓				✓							✓
Physical activity (IPAQ)		✓											✓
Depression (GDS)		✓											✓
Food Frequency Questionnaire (FFQ)		✓											✓
24-hour dietary recall		✓											✓
Nitrate: urine		✓*				✓†‡			✓‡				✓*
Salt: urine		✓*				✓†‡			✓‡				✓*
Cognitive performance		✓											✓
Resting blood pressure		✓				✓†			✓				✓
Body composition		✓				✓†§			✓§				✓
Physical function		✓											✓
Blood sample and dried blood spot		✓											✓
Saliva sample and salivary strips		✓	✓†¶	✓¶	✓

*Twenty-four hour urine and spot urine samples.

†Intervention groups only.

‡Spot urine sample only.

§Body weight only.

¶Saliva strips only.

FFQ, Food Frequency Questionnaire; GDS, Geriatric Depression Scale; IPAQ, International Physical Activity Questionnaire.

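### Table 1 schedules the medical-event and medication checks at week 8, when controls have no visit, and not at week 16, which all arms share; text and table also conflict on control-arm month-4 urine

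*Protocol article*

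**What the plan says.** **Visits.** The Study procedure section says: "An interim 2-month visit will take place for those in the intervention groups only". At that visit, besides a short adherence questionnaire, "body weight and resting blood pressure will be measured and salivary strip and spot urine samples will be collected". For month 4 it continues: "The same measurements and further dietary reinforcement messages will be conducted at an interim 4-month visit for the participants allocated to the intervention arms". For the control arm it then says: "Participants in the control arm will only have one interim visit at month 4 and will have their weight and blood pressure measured". The Outcome measures section describes the schedule more broadly: "Outcome assessments will be conducted at baseline, month 4 and month 6 for all groups, with an additional assessment visit at month 2", the month-2 visit being for the intervention groups.

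**Table 1 (Outcome measures).** The control group has one interim home visit, at week 16; the intervention groups have two, at weeks 8 and 16. The rows "Any medical events" and "Concomitant medication check list" are ticked at baseline, week 8 and week 24. Neither is ticked at week 16, and neither week-8 tick carries the dagger that restricts a cell to the intervention groups. The two urine rows (nitrate and salt) carry that dagger at week 8 but not at week 16, where the only mark is the one for spot urine.

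**Other capture.** Under Data monitoring, adverse events that participants report go into a register. No visit schedule is attached to it, and it does not mention medication.

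**The concern.** Two separate problems arise from the same schedule.

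First, the mid-trial check of events and medication falls at a visit that controls do not have and is missing from the visit that everyone has. Any summary of events or medication changes by arm would then partly reflect how often people were asked. Medication matters more than events here. Under Eligibility criteria, people on antihypertensive treatment may enter, while those whose regimen changed in the previous 3 months and regular users of several sodium-altering drug classes may not. The protocol thus treats medication as relevant to its outcomes, then schedules fewer checks for changes in the control arm. The blood-pressure effect sizes are meant to inform the sample size of the follow-on trial.

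Second, staff cannot tell whether controls give urine at month 4. If they do not, month-4 sodium and nitrate in the intervention arms have no concurrent comparator. Because this trial exists partly to test its own data-collection procedures, a flaw in the schedule could pass into the main trial.

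**Working it through.** No sample-size or power figure is involved. The check sets Table 1 beside the text and counts.

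**Inputs.** 120 participants in four arms (Study design), 30 per group (Sample size): 3 × 30 = 90 intervention and 30 control. Tick positions are from Table 1. All rows used below fill all 13 columns, so each tick can be placed.

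| Table 1 row | Week 8 | Week 16 | Week 24 |
|---|---|---|---|
| Home visit, intervention | yes | yes | – |
| Home visit, control | no | yes | – |
| Medical events | tick, no dagger | blank | tick |
| Medication checklist | tick, no dagger | blank | tick |
| Urine (nitrate; salt) | intervention only, spot | spot, no arm restriction | 24-hour and spot |
| Blood pressure | intervention only | no arm restriction | tick |
| Body composition | intervention only, weight | weight, no arm restriction | tick |

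(Week 24 is the end-of-study visit for all arms, not a home-visit row.)

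**Scheduled post-baseline checks per person.** Intervention: weeks 8 and 24 = 2. Control: week 24 = 1. The undaggered week-8 ticks imply a control check with no visit at which to do it.

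**Longest interval between scheduled checks**, using the column labels (baseline is labelled week 1). Intervention: 24 − 8 = 16 weeks. Control: 24 − 1 = 23 weeks.

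**Month-4 urine.** The dagger is used consistently: blood pressure and weight carry it at week 8 and drop it at week 16, which agrees with the text, since controls are measured for both at month 4. By the same convention the week-16 urine cells include controls. The text gives controls weight and blood pressure, and assigns the repeat of the month-2 set, which includes spot urine, to the intervention arms. Before dropout, planned month-4 spot urines are therefore 90 + 30 = 120 by the table and 90 + 0 = 90 by the natural reading of the text.

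**Recall period if the checks are added at week 16.** If staff ask about the time since the last visit, intervention participants report on 16 − 8 = 8 weeks and controls on 16 − 1 = 15 weeks, which is a new imbalance. If they ask about the time since baseline, both report on 15 weeks. From week 16 to week 24 the period is 8 weeks in every arm.

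**The case against.** The case for leaving this alone has real weight.

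- All arms complete both checklists at week 24, when final blood pressure is taken. The difference is one extra interim check. A reader might infer that events in controls go unrecorded; the documents do not support that, given the week-24 check and the participant-reported register. The register does not, however, cover medication.
- Event and medication counts are not listed as primary or secondary outcomes, and Statistical analysis names no between-arm test of them. The protocol calls its comparative analysis exploratory. This stands and limits the severity.
- The eligibility exclusions narrow the room for medication changes. In-trial changes remain possible, and nothing in the document allows an estimate of how many a week-24 check would miss.
- The text never says outright that controls give no samples: in the control-arm sentence, the word only qualifies the number of visits. A missing dagger in Table 1 would explain the mismatch equally well. So the documents do not show which version is right, only that they differ. The statement that month-4 assessments cover all groups does not settle what those assessments include.
- A reader might go further and say that the extra contact biases the factorial effects: "The intervention groups will also receive bi-weekly text message reminders", and controls do not. The documents do not support treating this as an error. Counselling, texts and reinforcement visits are the intervention, written general advice is the chosen comparator, and no size for a contact effect can be drawn from the protocol.
- A reader might also extend the conflict to salivary strips. The saliva row of Table 1 is damaged in the copy available (5 cells of 13), so nothing here rests on it.

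**Conclusion.** The point holds in two limited parts. As scheduled, intervention participants have two post-baseline checks of events and medication and controls have one, with longest intervals of 16 and 23 weeks. Text and table also disagree on whether up to 30 controls give spot urine at month 4.

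Severity is low. The week-24 comparison of events, medication and biomarkers is intact in all arms, and between-arm analysis is exploratory. What is affected is the evenness of medication-change recording behind the blood-pressure estimates, any by-arm summary of events, and the month-4 adherence comparison.

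This assumes that Table 1 is followed as printed, that the unmarked week-8 checks are done only where a visit exists, and that there is no dropout. It does not claim that any effect estimate is biased by a known amount.

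**What to change.** 1. **Add both checklists to the existing week-16 visit in all four arms.** Ask about the period since baseline, or record onset and change dates, so that the recall period is the same in every arm.
2. **Mark the week-8 checks in Table 1 as intervention-only.** Base any between-arm summary on the common week-16 and week-24 checks. Do not discard events or changes first reported at week 8: carry them forward with their dates, and record the visit of first report so that any help from the earlier check is visible.
3. **Reconcile the Study procedure text with Table 1 on control-arm month-4 urine.** Either version would remove the contradiction. Collecting spot urine from controls at week 16 is preferable, because month-4 sodium and nitrate then have a concurrent comparator. If it is not collected, add the dagger to the week-16 urine cells and describe month-4 adherence within the intervention arms only.

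**Cost.** Two short checklists at up to 120 visits that already take place. If control urine is collected, up to 30 further spot samples and their sodium and nitrate assays (30 × 2 = 60), with a minor added burden on controls. No new visit is needed.
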